## Abstract

**Background:**

Filgotinib (FIL), a Janus kinase-1 preferential inhibitor, has been studied for its efficacy and safety in rheumatoid arthritis. The FINCH3 trial compared FIL monotherapy, FIL plus methotrexate (MTX) combination therapy, and MTX monotherapy in MTX-naïve patients. However, comparisons in patients with an inadequate response to MTX remain unclear. This study aims to evaluate the efficacy and safety of FIL plus MTX versus FIL monotherapy in patients with rheumatoid arthritis who have an inadequate response to MTX.

**Methods and analysis:**

FAITHFUL (**F**ilgotinib **A**dd-on versus sw**IT**c**H** to **F**ilgotinib in patients with rhe**U**matoid arthritis who inadequate**L**y responded to methotrexate) study is a phase IV multicenter, prospective, open-label, randomized controlled trial. Patients with a history of inadequate response to at least 8 weeks of MTX and moderate or high disease activity will be assessed for eligibility at 10 centers in Japan. A history of Janus kinase inhibitor use is an exclusion criterion, but prior use of biologic agents is not considered. Enrolled patients will be randomly assigned in a 1:1 ratio to either the group adding FIL (Add-on group) or the group switching to FIL monotherapy (Switch group). The target sample size is 120 participants. The primary endpoint is the change in DAS28-CRP from baseline to week 24, aiming to assess if the Switch group is non-inferior to the Add-on group. Safety will be evaluated by assessing the incidence of adverse events.

**Ethics and dissemination:**

The study has received approval from the Certified Review Board of Keio University Hospital (N20230002) and adheres to the principles outlined in the Declaration of Helsinki and good clinical practice standards. Prior to enrollment, all participants provide written informed consent. The findings from this study are intended to be submitted for publication in relevant peer-reviewed journals.

**Trial registration:**

The trial was registered at Japan Registry of Clinical Trials (jRCTs031230673).

## Introduction

Rheumatoid arthritis is an autoimmune disease that primarily affects the joints, which can result in joint pain, swelling, stiffness and, eventually, joint damage and deformities [1,2]. The prevalence of rheumatoid arthritis is estimated to be around 1% worldwide [1]. The peak onset of rheumatoid arthritis typically occurs in individuals in their 40s and 50s, an age associated with peak social productivity. This can lead not only to physical disability but also to significant social limitations, economic burden, and psychological distress. If left untreated, approximately 70% of patients will develop bone erosions within 2 years [3]. Therefore, early and effective treatment intervention is fundamentally essential.

Disease-modifying antirheumatic drugs (DMARDs) are used to improve the clinical symptoms and prevent joint damage in patients with rheumatoid arthritis. The 2022 update of European League Against Rheumatism (EULAR) recommendations suggest that, unless contraindicated, treatment should begin with methotrexate (MTX), aiming to achieve clinical remission or at least low disease activity within 3–6 months [4]. If this goal is not reached, the addition of biological DMARDs (bDMARDs) or targeted synthetic DMARDs is recommended [4].

Filgotinib, a Janus kinase-1 preferential inhibitor, is one of the targeted synthetic DMARDs and has been evaluated for its efficacy and safety in the treatment of rheumatoid arthritis. The DARWIN1 and DARWIN2 studies were phase II trials that investigated the combination therapy of filgotinib and MTX, and the efficacy of filgotinib monotherapy, respectively, in patients with rheumatoid arthritis with an inadequate response to MTX [5,6]. Both studies showed positive results in the primary endpoint, which was the American College of Rheumatology (ACR) 20 improvement rate at 12 weeks. However, neither trial directly compared the combination therapy of filgotinib and MTX with filgotinib monotherapy. The FINCH1 trial was phase III study that assessed the efficacy and safety of the combination therapy of filgotinib and MTX in patients with moderate to severe active rheumatoid arthritis who had an inadequate response to MTX [7]. The FINCH2 trial evaluated the efficacy and safety of the combination therapy of filgotinib and conventional synthetic DMARDs (csDMARDs) in patients with moderate to severe active rheumatoid arthritis who had an inadequate response or were intolerant to biologic agents [8]. Both the FINCH1 and FINCH2 trials did not directly compare the combination therapy of filgotinib and MTX with filgotinib monotherapy. In the FINCH3 trial, the combination of filgotinib and MTX was compared to filgotinib monotherapy [9]. However, the trial included patients who had never been treated with MTX, so it did not directly compare the therapies in patients who had not responded to standard treatments, such as MTX or MTX combined with bDMARDs. Thus, it remains unknown whether filgotinib monotherapy and the combination of filgotinib and MTX are equally effective and safe in patients with an inadequate response to MTX.

Randomized controlled trials comparing the combination of tocilizumab and MTX with a switch to tocilizumab monotherapy in rheumatoid arthritis patients with an inadequate response to MTX have reported a higher incidence of liver dysfunction in the combination therapy group [10,11]. Additionally, long-term MTX use is associated with various complications, such as hepatotoxicity, bone marrow suppression, and lymphoproliferative disorders. Given that filgotinib is effective even without MTX, filgotinib monotherapy is expected to offer a safer treatment option while maintaining efficacy in patients with rheumatoid arthritis who do not respond adequately to MTX. Therefore, we aim to compare the efficacy and safety of filgotinib monotherapy with the combination therapy of filgotinib and MTX in patients with moderate to severe active rheumatoid arthritis who had an inadequate response to MTX.

## Materials and methods

### Trial design

FAITHFUL (**F**ilgotinib **A**dd-on versus sw**IT**c**H** to **F**ilgotinib in patients with rhe**U**matoid arthritis who inadequate**L**y responded to methotrexate) is a multicenter, open-label, randomized, controlled, investigator-initiated non-inferiority trial conducted at 10 rheumatology centers in Japan (Fig 1 and 2). Patients with rheumatoid arthritis who have an inadequate response to MTX or bDMARDs combined with MTX will be randomly assigned, in a 1:1 ratio, to either the group adding filgotinib (Add-on group) or the group switching to filgotinib monotherapy (Switch group). MTX will be maintained at the same dose as at enrollment unless clinically significant adverse events occur. bDMARDs and csDMARDs will be discontinued at the start of filgotinib administration. The primary endpoint is the change in disease activity score 28 (DAS28)-C-reactive protein (CRP) from baseline at week 24. After week 24, patients in the Add-on group may reduce or discontinue MTX if desired and agreed upon by the attending rheumatologist, while patients in the Switch group may resume MTX administration.

**Fig 1 pone.0322621.g001:**
[figure not shown]
SPIRIT schedule. Common laboratory tests include white blood cell count, white blood cell differential (eosinophils, basophils, neutrophils, lymphocytes, atypical lymphocytes, monocytes), red blood cell count, hemoglobin, mean corpuscular volume, platelet count, erythrocyte sedimentation rate, blood urea nitrogen, creatinine, uric acid, total bilirubin, aspartate aminotransferase, alanine aminotransferase, lactate dehydrogenase, gamma-glutamyl transferase, alkaline phosphatase, C-reactive protein, total protein, albumin, immunoglobulin G. Baseline X-ray examinations of the hands and feet can use results obtained within 12 weeks prior. X-ray examinations of the hands and feet are not required at the time of discontinuation if the discontinuation occurs within 28 days of the previous X-ray examination. Abbreviation: VAS: Visual Analog Scale; HAQ: Health Assessment Questionnaire; WPAI: Work Productivity and Activity Impairment; MMP-3: Matrix Metalloproteinase-3; RF: Rheumatoid Factor; CRP: C-reactive Protein; ESR: Erythrocyte Sedimentation Rate; LDL: Low-Density Lipoprotein; HDL: High-Density Lipoprotein; TG: Triglycerides; SDM: Shared Decision-Making; FIL: Filgotinib; MTX: Methotrexate.

**Fig 2 pone.0322621.g002:**
[figure not shown]
Study design. At 24 weeks, SDM determines whether to discontinue or initiate MTX. In the FIL + MTX group, MTX may be discontinued, whereas in the FIL group, MTX may be added if deemed necessary. Abbreviation: MTX-IR, methotrexate-inadequate response; FIL, filgotinib; SDM, shared decision making; DAS28-CRP, disease activity score 28-C-reactive protein.

### Eligibility criteria

Eligible patients are those who satisfy all the inclusion criteria and do not meet any of the exclusion criteria.

### Inclusion criteria

1) Patients aged 18 years or older2) Patients diagnosed with rheumatoid arthritis based on the 1987 ACR classification criteria or the 2010 ACR/EULAR classification criteria3) Patients who have received stable treatment with MTX at a dose of at least 6 mg/week or combination therapy with bDMARDs and MTX for at least 8 weeks prior to enrollment but still demonstrate moderate to high disease activity, defined by a DAS28-CRP score of 3.2 or higher4) Patients with at least 2 tender joints and at least 2 swollen joints5) Patients who have not previously used JAK inhibitors6) Patients may receive glucocorticoids at a dose equivalent to 10 mg/day or less of prednisolone7) Patients who have provided written consent to participate in this study

### Exclusion criteria

1) Patients who plan to become pregnant or give birth between the time of consent and the completion of study treatment2) Patients with an estimated glomerular filtration rate less than or equal to 30 mL/min/1.73 m²3) Patients with aspartate aminotransferase or alanine aminotransferase levels exceeding five times the upper normal limit4) Patients with a white blood cell count below 2000/μL5) Patients with a platelet count below 100,000/μL6) Patients with a history of venous thromboembolism within 2 months prior to obtaining consent7) Patients with a history of acute interstitial pneumonia within 2 months prior to obtaining consent8) Patients with a history of herpes zoster within 2 months prior to obtaining consent9) Patients with a history of hypersensitivity to either filgotinib or MTX components10) Patients who are breastfeeding11) Patients with pleural effusion, ascites, or other similar conditions12) Patients with active tuberculosis13) Patients deemed unsuitable for participation in the study by the principal investigator or sub-investigator

### Withdrawal criteria

Subjects must be withdrawn from the study if they meet any of the withdrawal criteria listed below. Upon withdrawal, subjects should undergo the specified assessments and tests for early termination. Additionally, the reason for withdrawal should be explained to the subject as appropriate, and post-withdrawal treatment should be provided in good faith to ensure the subject experiences no disadvantage. The principal investigator or sub-investigator must document the date and reason for withdrawal in the electronic data capture (EDC) system. For traceable subjects, their clinical course should be monitored and reported to the Study Secretariat. Subjects withdrawn from the study will not be replaced, regardless of the reason for withdrawal.

1) Subject wishes to discontinue his/her study treatment2) Subject wishes to withdraw his/her consent3) Serious (or significant) adverse event occurs, and the study treatment is determined to be difficult to continue4) A comorbidity (complication, etc.) exacerbates, and the study treatment is determined to be difficult to continue5) If the study treatment is interrupted for more than 28 consecutive days6) Confirmed pregnancy7) If a significant protocol deviation is identified and it is determined that continuing the study would be inappropriate8) If it is discovered after enrollment that the subject does not meet the inclusion criteria or violates the exclusion criteria, and it is determined that continuing the study would be inappropriate9) If, for any other reason, the principal investigator or sub-investigator determines that continuing the study is not appropriate

### The status and timeline of the study

This trial was registered at Japan Registry of Clinical Trials (jRCTs031230673) in March 2024. Currently enrollment is ongoing.

Enrollment period: Publication date of the implementation plan – September 2025 (18 months).

Intervention period: 48 weeks

Data collection, analysis, and report generation periods: 2 years

First patient first visit: April 2024

Last patient first visit: September 2025

Last patient last visit: September 2026

Data collection and Fix: March 2027

Analysis and Clinical Study Report: September 2027

Total study period: 3 years and 6 months

### Allocation and blinding

A minimization method is used with history of bDMARDs use (yes/no) and anti-cyclic citrullinated peptide antibody status (positive/negative). Eligible patients will be randomly assigned electronically by a central system in a 1:1 ratio to either the combination therapy group (Add-on group) or the group switched to filgotinib monotherapy (Switch group). This is an open-label trial with no blinding implemented.

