### Outcomes

#### Primary endpoint.

The primary endpoint is the change in DAS28-CRP from baseline at week 24, with the objective of determining if the Switch group is non-inferior to the Add-on group. The non-inferiority margin of 0.6 was adopted based on the study by Rubbert-Roth et al [12]. The value of 0.6 was derived by Rubbert-Roth and colleagues based on the meta-analysis results of treatment effects using DAS28 in patients with rheumatoid arthritis, as well as the fact that a change of 0.6 or less is internationally adopted in the EULAR response criteria as a threshold indicating no clinically significant change [13].

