#### Secondary endpoints.

1) Remission achievement rate

The rate of achieving remission at each time point based on DAS28-CRP, Simplified Disease Activity Index (SDAI), Clinical Disease Activity Index (CDAI), and Boolean criteria will be analyzed. The denominator for the proportion will be the number of full analysis set (FAS) in each group, and subjects who discontinue early will be considered as non-achievers. The definition of remission is as follows: DAS28-CRP < 2.6, SDAI ≤3.3, CDAI ≤2.8, Boolean criteria with ≤1 for all of the following items: tender joint count, swollen joint count, patient visual analog scale (VAS), and CRP.

2) Low disease activity achievement rate

The rate of achieving low disease activity at each time point based on DAS28-CRP, SDAI, and CDAI will be analyzed. The denominator for the proportion will be the number of FAS in each group, and subjects who discontinue early will be considered as non-achievers. The definition of achieving low disease activity is as follows: DAS28-CRP ≤ 3.2, SDAI≤11, and CDAI≤10.

3) Change from baseline in DAS28-CRP, SDAI, and CDAI

Change from baseline in DAS28-CRP, SDAI, and CDAI at each time point will be analyzed.

4) ACR20/50/70 and ACR-N achievement rates

Achievement rates of ACR20, ACR50, and ACR70, as well as ACR-N at each time point, will be analyzed. For ACR20, ACR50, and ACR70, the denominator for the proportion will be the number of FAS in each group, and subjects who discontinue early will be considered as non-achievers.

5) Functional remission achievement rate

The rate of achieving functional remission in Health Assessment Questionnaire (HAQ) at each time point will be analyzed. The denominator for the proportion will be the number of FAS in each group, and subjects who discontinue early will be considered as non-achievers. Functional remission is defined as HAQ ≤ 0.5.

6) Structural remission achievement rate

The rate of achieving structural remission in modified Total Sharp Score (mTSS) at week 24 and week 48 will be analyzed. The denominator for the proportion will be the number of FAS in each group, and subjects who discontinue early will be considered as non-achievers. Structural remission at both week 24 and week 48 is defined as an mTSS progression of ≤0.5.

7) Clinical relevant radiographic progression (CRRP, ΔmTSS ≥3) and rapid radiographic progression (RRP, ΔmTSS ≥5) rates

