The rate of CRRP and RRP at week 24 and week 48 will be analyzed. The denominator for the proportion will be the number of FAS in each group, with the numerator for the CRRP rate being the number of cases with an mTSS increase of 3 or more at week 24 and 48, and the numerator for the RRP rate being the number of cases with an mTSS increase of 5 or more at week 24 and 48.

8) Cumulative values of CRP and matrix metalloproteinase (MMP)-3

The cumulative values of CRP and MMP-3 will be analyzed, with definition as the area under the curve (AUC) for CRP and MMP-3 for each subject.

9) Work productivity and activity impairment (WPAI)

WPAI at week 24 and week 48 will be analyzed. At week 24, summary statistics will be calculated for baseline values, measurements at each time point (week 24 and week 48), and changes from baseline in the two groups (Add-on group and Switch group). At week 48, the analysis will include four groups (Add-on to Switch group and Switch to Add-on group in addition to the original two groups).

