Independent monitors will visit the study sites to examine the records, verify them against source documents, and engage with the investigators and site coordinator to observe and discuss the trial’s progress. They are responsible for ensuring compliance with the protocol and guidelines, as well as overseeing the completion of the electronic Case Report Form (eCRF) and other required documentation.

This study is a collaborative research project with Gilead Sciences, Inc., the manufacturer of JYSELECAⓇ (filgotinib). Gilead Sciences, Inc. will be involved in the preparation of the study protocol. However, Gilead Sciences, Inc. will not participate in data collection, data management, statistical analysis, or the evaluation of study results. Therefore, audits are not considered mandatory, and routine audits will not be conducted. The reliability of this study is ensured by the fact that it is not a clinical trial aimed at regulatory approval. Monitoring will be implemented to protect study participants, ensure ethical standards, adhere to clinical research laws and the study protocol, and maintain data reliability and appropriate research practices.

In this study, both central monitoring and on-site monitoring will be conducted. Central monitoring will be performed every six months in principle. It will include the review of progress management items (enrollment progress and status of discontinued cases), safety management items (compliance with the study protocol and the presence or absence of adverse events), and outcome-related items (the implementation status of the primary endpoint, secondary endpoints, and efficacy assessment items). On-site monitoring will be conducted twice: once within three months after the enrollment of the first patient at each site and once after treatment completion or after the enrollment of the last patient at each site. The monitoring will include confirmation of the informed consent process, eligibility of enrolled patients, and compliance with the study protocol with data accuracy.

The accuracy, consistency, and reliability of the data will be scrutinized through independent monitoring, which operates separately from the study investigators as noted above. Furthermore, a steering committee consisting of external experts, independent of the study investigators, will conduct a thorough review of the data.

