The study protocol defines multiple efficacy endpoints, including DAS28-CRP changes, ACR response rates, quality-of-life measures such as HAQ and WPAI, and radiological changes, indicating a comprehensive endpoint design. Safety endpoints are also robust, emphasizing AEs and laboratory abnormalities. Furthermore, allowing shared decision-making between patients and rheumatologists post-week 24 reflects a patient-centric approach, providing flexibility in tapering or restarting MTX based on clinical need. On the other hand, the limitation of this study is the lack of blinding which may introduce bias in subjective endpoints like patient-reported outcomes. However, this open-label design allows for a more practical evaluation of treatment effectiveness in a real-world setting, where patients and physicians are aware of the treatments being administered, potentially enhancing adherence and capturing a broader range of patient experiences.

In clinical trials, outcome measures are often repeatedly assessed in the same individuals over time, resulting in longitudinal data. However, it is common for participants to discontinue the study or miss scheduled visits, leading to incomplete or missing data. MMRM is a likelihood-based approach that provides valid estimates under the assumption of missing at random (MAR), without requiring data imputation. MMRM utilizes available data while accounting for baseline covariates and within-subject correlations, making it a robust method when the mean and covariance structures are correctly specified. However, as the missing data mechanism cannot be directly verified from observed data, and MMRM is only valid under MAR, it is important to consider alternative analytical approaches when its assumptions are not met. In this study, we acknowledge these limitations and will explore additional sensitivity analyses to ensure the robustness of our findings.

In conclusion, the FAITHFUL study protocol is well-designed to address an important clinical question in the management of rheumatoid arthritis. By leveraging a randomized, multicenter approach, the study could provide pivotal evidence on the viability of filgotinib monotherapy as an effective alternative for MTX-refractory patients.

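### The protocol states that no blinding is implemented and makes no exception for mTSS scoring, so the films behind the structural endpoints may be read with the treatment arm known

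*Protocol article*

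**What the plan says.** Allocation and blinding describes minimization and central 1:1 assignment, and ends: "This is an open-label trial with no blinding implemented". No assessor or film reader is exempted.

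Secondary endpoints then sets outcomes that rest on a scored radiograph. On structural remission it says "The rate of achieving structural remission in modified Total Sharp Score (mTSS) at week 24 and week 48 will be analyzed", and gives the cut-off: "Structural remission at both week 24 and week 48 is defined as an mTSS progression of ≤0.5". On progression of 3 or more (CRRP) and 5 or more (RRP) it says: "The rate of CRRP and RRP at week 24 and week 48 will be analyzed". Other efficacy endpoints adds change in mTSS. The legend to Fig 1 provides for hand and foot films at baseline and, with a 28-day exemption, at discontinuation.

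The Discussion concedes that "the limitation of this study is the lack of blinding which may introduce bias in subjective endpoints like patient-reported outcomes". Films are not mentioned there. Data management, monitoring, and auditing says that "a steering committee consisting of external experts, independent of the study investigators, will conduct a thorough review of the data", but gives neither that committee nor the monitors any part in reading films.

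**The concern.** Patients and treating physicians cannot be masked in this open-label comparison, but a person scoring stored films can be. The practical argument in the Discussion for an open-label design is that patients and physicians know the treatment, as in routine care. That gives no reason for a film reader to know the arm.

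The trial asks whether MTX can be dropped, and structural damage is one of the few efficacy outcomes that could be protected from knowledge of treatment. The 0.5-point cut-off for structural remission is tight, so a small shift in scoring changes a patient's class. Sample size calculation records a prior clinical assumption that monotherapy would not be inferior, so a reader who knows the arm could hold an expectation. The resulting bias could go in either direction.

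**Working it through.** **1. Who is masked, according to the document.**

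| Place | What it settles | What it leaves open |
|---|---|---|
| Allocation and blinding | Open-label; no blinding; no exception | Whether the sentence is meant to cover film readers |
| Secondary endpoints; Other efficacy endpoints | Four mTSS outcomes, with cut-offs 0.5, 3 and 5 for the three rates | Who scores, how many readers, central or local, what they see, film order |
| Data management, monitoring, and auditing | Independent monitors; external committee reviews data | Any masked reading |
| Discussion | Bias conceded for subjective endpoints, with patient-reported outcomes as the example | Whether films are included |

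Read literally, the first row leaves films unmasked, and no later row restores masking. Nothing states that a reader will know the arm.

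**2. The primary endpoint and sample size.** The Primary endpoint section reads: "The primary endpoint is the change in DAS28-CRP from baseline at week 24, with the objective of determining if the Switch group is non-inferior". It uses no film. The stated sample size reproduces from the margin 0.6, assumed difference 0.07, SD 1.1, one-sided 0.05 and 80% power:

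n per group = 2 × [1.1 × (1.645 + 0.842) / (0.6 − 0.07)]² = 53.26, rounded up to 54, so 108 in total. With 10% dropout, 108 / 0.9 = 120.

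No input depends on how films are read.

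**3. Effect of one changed classification.** With 60 per group, 1/60 = 1.7 percentage points in that arm's rate.

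**4. Illustration only.** The document gives no structural remission rate and no misclassification rate, so both are assumed. Let true remission p be equal in both arms, and let a reader who knows the arm move a share m of one arm's non-remission films across the cut-off. The false difference is Δ = m(1 − p). With p̄ the mean of p and p + Δ, and n = 60, the chance that a two-sided 5% comparison shows a difference in that direction is

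Φ{[Δ − 1.96·√(2p̄(1−p̄)/n)] / √[p(1−p)/n + (p+Δ)(1−p−Δ)/n]}.

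| p | m | Δ (points) | Chance (nominal 2.5%) |
|---|---|---|---|
| 0.6 | 0.1 | 4 | 6.6% |
| 0.6 | 0.3 | 12 | 28.2% |
| 0.8 | 0.1 | 2 | 4.6% |
| 0.8 | 0.3 | 6 | 13.8% |

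These values are somewhat high. Early discontinuers count as non-achievers whatever a reader scores. If 10% of an arm (6 of 60) discontinue, then at p = 0.6 only 24 − 6 = 18 non-achievers have a film that can change class, and m = 0.3 gives 5.4/60 = 9 points instead of 12. At p = 0.8 there are 12 − 6 = 6, and m = 0.1 gives 0.6/60 = 1 point instead of 2. Each Δ follows directly from the assumed m, so the table shows how sensitive the rate is and does not estimate the bias.

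**The case against.** The strongest objection is that the sentence closes a paragraph on treatment assignment and may describe treatment masking only. A journal article condenses a full protocol, and reader number, film coding and masking are commonly left to that document or to an imaging manual. On that view the article is merely silent about readers.

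Part of this stands. A reader might infer that the films will be scored with the arm known; the document does not support that, because it never says who reads them. What remains is that the article makes an unqualified statement: open-label already covers treatment, and the words that follow exclude blinding altogether. If readers are masked under a procedure not shown, the sentence is wrong as written. If they are not, an avoidable bias is permitted. Either way it needs correcting.

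Three further objections are fair:

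- A reader might infer that the limitation in the Discussion excludes radiographs. It gives patient-reported outcomes only as an example, so all that can be said is that films are not named.
- Masking might be called nearly free. No cost is given in the document, and local scoring at 10 centers would mean moving films.
- The consequence is limited. These are secondary and other endpoints. For secondary proportions, Statistical methods plans rates with 95% confidence intervals and names no between-group test. After week 24 patients in either arm may change MTX, so the week-48 contrast is diluted whether or not films are masked. Week 24 is the cleaner comparison.

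**Conclusion.** The point holds as a correctable weakness in a stated rule. The plan says that no blinding is implemented, makes no exception for mTSS scoring, and provides masked reading nowhere else. As written, it permits the films behind structural remission, CRRP, RRP and mTSS change to be scored with the arm known. It does not show that they will be.

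The size of any bias cannot be estimated from the document. The only firm figure is 1.7 percentage points per reclassified patient in an arm of 60; any larger figure rests on an assumed share of films moved. The primary non-inferiority conclusion and the sample size are not touched. The change is worth making because it removes an avoidable source of bias without altering visits, treatment or the primary analysis.

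**What to change.** Amend Allocation and blinding to say that treatment is open-label but that mTSS readers are masked to treatment arm. Have them score coded films from baseline, week 24, week 48 and discontinuation, and state whether film order is hidden. If masking is not feasible, name radiographic scoring in the limitation in the Discussion, beside patient-reported outcomes.

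The cost is coding the films and, if sites would otherwise score their own patients, exchanging or pooling films among the 10 centers. Masking in itself requires no additional film, visit or reader. By the stated timeline, the last patient visit is in September 2026 and data are fixed in March 2027. Films can be coded before scoring, and any already scored with the arm known can be re-read in coded form.
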